#### 2.5.3 Covariates for SS2.

***Physical education (PE):*** Information on PE (binary variable: yes/no on a daily basis) during their participation in the study was collected though school timetables.

***Transportation to/from the school garden:*** Information on which transport mode; walking, biking, train, bus, or a combination, will be obtained from the responsible teachers, and used as a categorical variable.

***Weather data:*** Data on general type of weather conditions, i.e., sun, rain, wind, thunder or snow, during school garden days will be collected from the Danish Metrologic Institute [66], and included as a categorical variable

***Size of the school garden plot:*** The plot size of the various school gardens will be measured in km^2^ through the Geographic Information System and included as a scale variable [67].

#### 2.5.4 Sample size.

In SS2, a subsample of the intervention group containing 45–55 classes will be recruited based on the former estimate calculation described in section 2.4.4 This number of classes was chosen in terms of resources, practicality, and distance to the school gardens. However, school gardens from both rural and urban areas will be included to secure representativity in the sub-sample. Based on previous similar Danish school intervention studies, the estimated drop-out during the intervention is 7 pct. of classes, corresponding to four classes. Including the minimum of 45 classes with an estimated average of 18 pupils per class will provide 11.340 days with PA data from accelerometer based on 810 children since data is based on seven days with two measurements. A previous study has found statistically significant positive associations between EOtC-sessions and PA on an even smaller sample adopting the same design [12], which indicates that a sample of 18 pupils per class will be sufficient.

#### 2.5.5 Statistical analysis.

All analysis will be conducted in the statistical program RStudio (version 1.4.1106; RStudio, Inc.) [68]. Linear mixed models taking into account the clustered nature of data with days clustered in pupils clustered in classes will be conducted to test differences between the pupils’ PA, basic psychological needs satisfaction, and intrinsic motivation on days with the school garden program and usual school days. Two-tailed tests with p-values below 0.05 will be considered statistically significant. All analyses will be adjusted for gender, and SES. Additionally, analyses adjusted for physical education, size of school garden and transport to/from the school garden will be applied in relevant sub-analysis.

The models are expressed as follows:

$$\begin{array}{l} Acute\;SM:\\ \text{Mean acute SM}(\text{Y})=({\text{β}}_{0}+{\text{b}}_{\text{class}}+{\text{b}}_{\text{id}})+{\text{β}}_{1}*\text{school\_schoolgarden}+{\text{β}}_{2}*\text{gender}+{\text{β}}_{3}*\text{SES}+\text{ε} \end{array}$$

$$\begin{array}{l} Acute\;PA:\\ \text{Mean PA}(\text{Y})=({\text{β}}_{0}+{\text{b}}_{\text{class}}+{\text{b}}_{\text{id}})+{\text{β}}_{1}*\text{school\_schoolgarden}+{\text{β}}_{2}*\text{gender}+{\text{β}}_{3}*\text{SES}+{\text{β}}_{4}*\text{weather}+\text{ε} \end{array}$$

Explanation for model concept for effects on acute SM and PA:

Y = The dependent variable (outcome) being analyzed, such as a score after the intervention.β_0_ +b_class_ + b_id_ = The intercept of the model.β_0_ represents the fixed intercept, which is the expected value of Y when all predictor variables are set to zero.β_class_ is the random intercept for class, which accounts for potential similarities among pupils within the same class.β_id_ is random intercept for individuals within each class, capturing within-class variation.β_1_ * school_schoolgarden = The effect of being in a school garden versus a regular school day.β_1_ represents the difference in Y between school garden days and school days.β_2_ * gender = The effect of gender.Gender is coded as a categorical variable (0 = boy, 1 = girl, 2 = other), β_3_ represents the difference in Y (outcome) between genders (boy, girl or other).β_3*_ SES = The effect of socioeconomic status (SES).β_3_ shows how changes in SES impact Y.β_4*_ weather = the effect of weather.β_4_ shows how weather conditions influence Y.ε = The residual error term, capturing unexplained variation in Y.

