### 2.1 The Gardens to Bellies program

The Danish school garden program GtB will serve as an intervention in this study (see the FoodACT study Logic Model, Fig 4). The GtB program is an ongoing educational initiative launched in 2006. School classes are invited to attend eight sessions (whole school days) in the school gardens (ten sessions/days in a few select municipalities) over the course of the second semester of fourth grade and the first semester of fifth grade (pupils approx. ten years of age, range nine to twelve). The school garden sessions start each year in March and end in October. Before the first school garden visit, an introductory workshop of one to two hours is conducted at the schools to spike the pupils’ curiosity. The school gardens are currently located in nine municipalities across Denmark. All participating school classes attend a school garden located in their own or near their own municipality, hence, the distance to the school garden as well as their mode of transportation to and from the school garden may vary across the participating schools. Furthermore, the plot size of the gardens varies across the garden locations.

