### 2.5 Sub-study 2: Physical activity and movement behavior in the school gardens

#### 2.5.1 Design.

A within-subject design will be applied for investigating whether, and to what extent, the pupils’ PA and acute SM are different in the school gardens compared to teaching as usual (i.e., classroom-based teaching). PA will be measured using accelerometry for two weeks out of which the pupils will attend the school garden one day. The pupils’ experience of basic psychological needs satisfaction, intrinsic motivation, and perception of the learning environment on school garden days and days with teaching as usual will be measured using an electronic survey distributed by a text-message to the parents on days they attend the school garden and on usual schooldays, in total seven days simultaneously with measuring PA.

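### The SS2 models have no class-by-day term, so any variation that a class shares on a day makes the standard error of the garden-day effect too small

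*Protocol article*

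**What the plan says.** All references are to the protocol article.

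- **Who attends and when.** Section 2.1: "School classes are invited to attend eight sessions (whole school days) in the school gardens". Section 2.5.1: "PA will be measured using accelerometry for two weeks out of which the pupils will attend the school garden one day". Day type is therefore fixed for a whole class on a calendar date.
- **Model structure.** Section 2.5.5, on the linear mixed models: "days clustered in pupils clustered in classes will be conducted to test differences". The class term "is the random intercept for class, which accounts for potential similarities among pupils within the same class"; the pupil term "is random intercept for individuals within each class, capturing within-class variation". Apart from the residual, the two printed equations have no other random term.
- **Fixed terms.** Both models contain day type, gender and SES. The physical activity (PA) model adds weather; the acute school motivation (SM) model does not. Physical education, plot size and transport are kept for sub-analyses.
- **Differences between gardens.** Section 2.1 says that "the distance to the school garden as well as their mode of transportation to and from the school garden may vary" across schools, and that plot size differs too.
- **Sample and test.** Section 2.5.4 counts at least 45 classes of 18 pupils on average, 810 children and 11,340 accelerometer days. Tests are two-sided at 5%.

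**The concern.** The description treats each pupil's days as that pupil's own. In fact the roughly 18 pupils of a class go through the same days together, so days are crossed with pupils within class. On a garden day they share the tasks, the facilitator and the journey; on a usual day they share the timetable.

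The class and pupil intercepts do not change from day to day, so both cancel from the garden-minus-usual comparison. Whatever a class has in common on a given day is left in the residual, which the model takes as independent between pupils. Nor does the model let the garden-day effect differ between classes, although the article expects conditions to differ between gardens.

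At stake are the standard errors, p-values and confidence intervals for the PA outcomes, which test Hypothesis 2, and for the acute SM outcomes.

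**Working it through.** **The plan's own figures.** 45 × 18 = 810 children, and 810 × 7 × 2 = 11,340 days. Both agree with section 2.5.4.

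**Inputs.** From section 2.5.4: m = 18 pupils per class, J = 45 classes. From section 2.5.5: two-sided alpha 0.05. Assumed, because the article gives no value: rho = class-day variance / (class-day variance + residual variance), from 0.01 to 0.20.

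**Variance of the contrast.** Scale the within-pupil day-to-day variance to 1, and let S be the within-pupil sum of squares of the day-type indicator.

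- The printed model reports approximately 1 / (J × m × S).
- With shared class-days the true variance is (rho + (1 − rho)/m) / (J × S).
- The ratio is m × rho + 1 − rho = 1 + (m − 1) × rho = 1 + 17 × rho, the design effect (DE).

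The standard error is too small by sqrt(DE). The true type I error is 2 × (1 − Phi(1.96 / sqrt(DE))), and 810 pupils are worth 810 / DE independent ones for this contrast. For rho = 0.05, DE = 1 + 0.85 = 1.85, sqrt(DE) = 1.36, 1.96 / 1.36 = 1.44, and the error rate is 0.15.

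| Assumed rho | DE | SE too small by | Type I error | 810 / DE |
|---|---|---|---|---|
| 0 | 1.00 | 1.00 | 5% | 810 |
| 0.01 | 1.17 | 1.08 | 7% | 692 |
| 0.02 | 1.34 | 1.16 | 9% | 604 |
| 0.05 | 1.85 | 1.36 | 15% | 438 |
| 0.10 | 2.70 | 1.64 | 23% | 300 |
| 0.20 | 4.40 | 2.10 | 35% | 184 |

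**Simulation under no effect** (45 classes of 18, 2,000 runs per setting). The analysis with class and pupil intercepts only was run with 7, 10 or 14 days including one garden day, and with 14 days including two. Rejection rates were 4.0% to 6.5% at rho = 0, 22% to 25% at 0.10 and 33% to 36% at 0.20. The number of days and of garden days made little difference. A paired contrast on class means rejected in about 4% to 6% of runs in every setting.

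**Direct fit of the printed structure.** In two simulated data sets (10 days, one garden day, rho = 0.10), the mixed model reported standard errors of 0.0372 and 0.0365. The true value is sqrt((0.10 + 0.90/18) / (45 × 0.9)) = 0.0609.

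These figures cover shared class-day variation only. If the garden-day effect itself varies between classes, that adds to the understatement.

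**The case against.** - **The size is assumed.** This stands. With rho = 0 there is no inflation, and rho may differ between, say, sedentary minutes and rated autonomy. The only ICC in the article, 0.046 in section 2.4.4, is a between-class value for sub-study 1 and is a different quantity. A reader might infer that significance is overstated for every SS2 outcome; the documents support this only if class-day correlation or class variation in the effect exists.
- **Weather is in the PA model.** This is a partial answer. For PA, rho is what remains after weather. But weather enters as broad categories, section 2.5.3 describes its collection for garden days, and the acute SM model has no day-level term except day type. Adjustment for physical education, plot size and transport is planned only in sub-analyses.
- **Class is already a random effect.** It allows for classes that differ in overall level, not for what a class shares on one day.
- **The outcome is labelled a mean.** Averaging per pupil and day type does not help, because the garden-day value still carries the class's shared component.
- **There may be two garden days.** Section 2.5.4 can be read as two measurement windows. The simulation shows similar inflation in that case.
- **Effective sample size.** A reader might conclude that there are 45 independent observations instead of 810. That would need rho = 1; the assumed range gives 692 to 184.

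**Conclusion.** The point holds in conditional form. The printed SS2 models omit the level at which garden day is assigned, and the 5% criterion is not kept if any class-day variation remains. For assumed rho of 0.01 to 0.20 with 18 pupils per class, the standard error is too small by a factor of 1.08 to 2.10 and the type I error is about 7% to 35%. The direction follows from the design and the printed equations; the size rests on the assumed rho.

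Two further readings are not supported. Nothing here shows that the estimated garden-day difference is biased; only its precision is affected. And Hypothesis 2 in Table 1 concerns PA alone, so the acute SM results share the defect without being part of that hypothesis.

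**What to change.** In section 2.5.5, state that the pupils of a class share the same days, and change both SS2 models in one of these ways:

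- add a class-by-date random intercept, or a class-level random slope for school_schoolgarden, with inference based on the number of classes;
- keep the present models and use standard errors that are cluster-robust at class level; or
- analyse a class-level paired contrast of garden-day mean minus usual-day mean.

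One of these is enough. With one garden day per class, a class-by-date intercept and a class-level slope cannot be told apart on the garden day itself unless the class-date variance of usual days is assumed to apply there too, so the plan need not require both.

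The change is to the wording of the model. Class is already in the equations, and daily measurement supplies the dates. The cost is wider confidence intervals, by roughly the factors in the table if rho lies in the assumed range.

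### The two printed sub-study 2 models have no weekday or study-day term, so day-to-day change shared by pupils can be confounded with the school garden coefficient if garden days are unevenly placed

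*Protocol article*

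**What the plan says.** Section 2.5.1 of the protocol article sets up a comparison within pupils: "A within-subject design will be applied for investigating whether, and to what extent" activity and acute school motivation differ between garden and classroom days. On exposure it says "PA will be measured using accelerometry for two weeks out of which the pupils will attend the school garden one day". The motivation survey goes out "on days they attend the school garden and on usual schooldays, in total seven days simultaneously with measuring PA".

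Section 2.5.5 prints both models:

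- Acute school motivation: random intercepts for class and pupil, the garden-versus-school indicator, gender and SES.
- Physical activity (PA): the same terms plus weather.

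The text says that the indicator's coefficient, β1, "represents the difference in Y between school garden days and school days", and describes the term as the effect of being in a school garden. On covariates, "All analyses will be adjusted for gender, and SES". Beyond the equations, "Additionally, analyses adjusted for physical education, size of school garden and transport to/from the school garden will be applied in relevant sub-analysis". On testing, "Two-tailed tests with p-values below 0.05 will be considered statistically significant".

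Section 2.5.3 lists the sub-study 2 covariates: physical education (PE, yes/no per day, from timetables), transport, weather (described as collected for garden days) and plot size. Weekday, calendar day and study day are not among them. No section says on which weekday or study day the garden visit falls, or whether this differs between classes.

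**The concern.** Each pupil has one garden day in the window. Within a pupil, and within a class that visits together, the garden indicator therefore marks one weekday and one place in the sequence. Whatever moves all pupils' values on that weekday or at that place moves with the indicator.

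The planned adjustments do little about this:

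- Gender and SES are constant within a pupil, so they cannot correct a contrast made within pupils.
- The acute motivation model has no day-varying covariate except the exposure itself.
- Weather varies by day, but it is described only for garden days and is not a stand-in for weekday or sequence.
- PE carries part of the weekday timetable, but it enters only in sub-analyses and cannot capture early-wear reactivity or the effect of answering the same survey repeatedly.

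Hypothesis 2 and the acute motivation comparison both rest on β1. If shared day effects enter it, a difference between days could be reported as a garden effect, or a real garden effect could be masked.

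**Working it through.** **1. The plan's own count.** Section 2.5.4: 45 classes × 18 pupils = 810 pupils; 810 × 7 days × 2 = 11,340 days. This reproduces the stated figure. For the contrast between school days I assume 10 school days per window, so 810 × 10 = 8,100 pupil-days, with one garden day per class.

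**2. Bias from a weekday shift.** Assume no true garden effect and that Friday differs from the other weekdays by x. Let p be the share of garden days on Friday. The within-pupil contrast is the garden day minus the mean of the other nine days.

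- Garden day on Friday: x − x/9 = 8x/9.
- Garden day on another weekday: 0 − 2x/9 = −2x/9.
- Expected bias: p(8x/9) − (1 − p)(2x/9) = x(10p − 2)/9.

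| Share of garden days on Friday | x = 0.1 SD | x = 0.2 SD |
|---|---|---|
| 0% | −0.022 | −0.044 |
| 20% (even spread) | 0 | 0 |
| 60% | +0.044 | +0.089 |
| 100% | +0.089 | +0.178 |

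The values of x and p are assumptions. The bias is in whatever SD unit x is in, and a negative x reverses the signs.

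**3. Bias from the sequence.** Assume a first-day shift x that keeps a fraction e^(−2/3) ≈ 0.513 of its size on each following day.

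- Seven surveys, garden survey first: the six later days sum to 1.036x, so the bias is x(1 − 1.036/6) = 0.827x. For x = 0.1 to 0.3 SD this is +0.083 to +0.248 SD.
- Seven surveys, garden survey last: x(0.018 − 2.018/6) = −0.318x, or −0.032 to −0.095 SD.
- Ten wear days, garden on day 1: +0.088 to +0.265 SD; on day 6: −0.019 to −0.057 SD.
- Garden days evenly spread over positions: 0.

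**4. What the weekday bias does to the test.** In units of the within-pupil residual SD, the standard error of the contrast is √[(1/810)(1 + 1/9)] = 0.037. With 60% of garden days on Friday the bias is 0.044/0.037 = 1.2 standard errors for x = 0.1, and 0.089/0.037 = 2.4 for x = 0.2. The chance of |Z| > 1.96 is then about 22% and 67%. A simulation of 4,000 null trials per setting gave 22% and 65%. With even spread in expectation it gave 5% and 7%. With weekday terms in the model the rate was 4% to 5% and the bias about zero in all four settings.

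**5. What day terms do not cure.** If classes also have day-to-day variation of their own, weekday terms leave it untouched. With an assumed class-by-day variance of 2% to 5% of the total, the simulated false-positive rate was about 10% to 21% with weekday terms included.

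**The case against.** The strongest reply is that the harm depends on scheduling facts that the article does not give. With even spread the bias is zero, and nothing suggests that visits cluster on one weekday or early in the wear period. Every shift size and placement pattern above is assumed. The printed equations are also not the whole covariate set, since PE, garden size and transport come in through sub-analyses, and the article condenses a fuller plan. Nothing in the article is contradicted or miscalculated.

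Most of this stands, and it limits the point. A reader might infer that day-to-day change is in fact being credited to the garden, or that the false-positive rate is known to exceed 5%. The documents do not support either: placement is not stated, and the bias may be positive, zero or negative. Nor do they support two premises that come easily to mind. How a class's garden date is chosen is not described, and PA is given only as minutes per day, without saying whether this includes time after school.

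What does not stand is that the sub-analyses close the gap, or that this is only detail left to another document. The article states two models and a reading of their coefficient. PE covers part of a weekday pattern in secondary analyses only, and no listed covariate covers sequence. Unknown placement is itself a reason to include the terms.

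**Conclusion.** The point holds in conditional form. As printed, neither sub-study 2 model can separate a garden effect from weekday or study-day change shared by pupils, and the article does not say that garden days are spread so that this would not matter. If placement is uneven, β1 can be biased in either direction; if it is even, the bias is about zero.

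The size cannot be fixed from the documents. The bias of 0.044 to 0.089 SD rests on five assumptions: no true garden effect, a Friday shift of 0.1 to 0.2 within-pupil SD, 60% of garden days on Friday, 10 school days per window and no class-specific day variation. A reader might also infer that day terms would by themselves secure a 5% error rate. They would not, because variation specific to a class on a given day is a separate matter.

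**What to change.** Add two fixed effects to both equations in section 2.5.5: weekday (Monday to Friday, categorical) and study-day number (wear day for PA, survey number for acute motivation). β1 then compares garden and usual days at the same weekday and the same place in the sequence. Report a table of garden days by weekday and study day. If nearly all garden days share one position, state that the day effect cannot be separated from the garden effect and limit the claim accordingly.

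The cost is two amended equations and one table. Daily accelerometer and survey records should carry their dates, so no new data should be needed. The model loses a few degrees of freedom among about 8,100 pupil-days. For the weekday terms, the simulated standard error stayed at 0.037 with even spread and rose to about 0.040 with 60% of garden days on Friday. It would rise further if garden days sat on very few positions, which would correctly show how little the data can separate.

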### 2.6 Sub-study 3: Evaluation of implementation and mechanisms of impact

In SS3, the implementation and mechanisms of impact will be investigated by conducting a qualitative exploration of whether the GtB program activities have been implemented as intended, as well as how underlying mechanisms operating in the school gardens relate to the potential effects on FL and CCL [69]. SS3 will focus on how the GtB program induces change only in the outcomes of FL and CCL as these concepts, to the best of our knowledge, have not previously appeared in the school garden literature [18]. Comparatively, PA is a widely studied outcome in both school garden studies [1,18,22], and in EOtC studies overall, where SM is also a prevalent area of investigation [5,6]. The sub-study will follow the Medical Research Council’s framework on developing and evaluating complex interventions [44] and standards for evaluation mechanisms [70], and will thus go beyond asking whether the GtB program is effective, to also unpack how it works, contributes to change, and interacts with the context in which it is implemented. Consequently, implementation will be understood as “*an actively planned and deliberately initiated effort with the intention to bring a given intervention into policy and practice within a particular setting*” [71]^(p6).^ By viewing the implementation of the GtB and its intended effects as inherently embedded within a specific context [71], SS3 will focus on identifying contextual factors important to the delivery of the program in its various unique settings. Mechanisms of impact will be operationalized as “*underlying entities, processes, or structures which operate in particular contexts to generate outcomes of interest*” [70]^(p368).^ By investigating GtB as an instrumental case, SS3 will further aim to identify significant mechanisms driving or hindering the promotion of FL and CCL in pupils. This will contribute with insights into how and why outcomes are generated, and whether certain contextual conditions affect these processes. Moreover, adherence to the intervention will be investigated by monitoring the dose of the intervention by asking the garden facilitators whether the frequency and duration of the garden sessions were delivered as intended [69].

